## Abstract

**Background:**

Regular cognitive training can boost or maintain cognitive and brain functions known to decline with age. Most studies administered such cognitive training on a computer and in a lab setting. However, everyday life activities, like musical practice or physical exercise that are complex and variable, might be more successful at inducing transfer effects to different cognitive domains and maintaining motivation. "Body-mind exercises", like Tai Chi or psychomotor exercise, may also positively affect cognitive functioning in the elderly. We will compare the influence of active music practice and psychomotor training over 6 months in Mild Cognitive Impairment patients from university hospital memory clinics on cognitive and sensorimotor performance and brain plasticity. The acronym of the study is COPE (Countervail cOgnitive imPairmEnt), illustrating the aim of the study: learning to better "cope" with cognitive decline.

**Methods:**

We aim to conduct a randomized controlled multicenter intervention study on 32 Mild Cognitive Impairment (MCI) patients (60–80 years), divided over 2 experimental groups: 1) Music practice; 2) Psychomotor treatment. Controls will consist of a passive test–retest group of 16 age, gender and education level matched healthy volunteers.

The training regimens take place twice a week for 45 min over 6 months in small groups, provided by professionals, and patients should exercise daily at home. Data collection takes place at baseline (before the interventions), 3, and 6 months after training onset, on cognitive and sensorimotor capacities, subjective well-being, daily living activities, and via functional and structural neuroimaging. Considering the current constraints of the COVID-19 pandemic, recruitment and data collection takes place in 3 waves.

**Discussion:**

We will investigate whether musical practice contrasted to psychomotor exercise in small groups can improve cognitive, sensorimotor and brain functioning in MCI patients, and therefore provoke specific benefits for their daily life functioning and well-being.

**Trial registration:**

The full protocol was approved by the Commission cantonale d’éthique de la recherche sur l'être humain de Genève (CCER, no. 2020–00510) on 04.05.2020, and an amendment by the CCER and the Commission cantonale d'éthique de la recherche sur l'être humain de Vaud (CER-VD) on 03.08.2021. The protocol was registered at clinicaltrials.gov (20.09.2020, no. NCT04546451).

**Supplementary Information:**

The online version contains supplementary material available at 10.1186/s12877-022-03678-0.

## Background

### Normal aging and cognitive decline

In the context of a rapidly growing elderly population, interventions that may slow down cognitive decline and support the maintenance of independence in the elderly are crucial for senior care and determining appropriate social, economic, and public health management. Age-related cognitive decline impacts particularly processing speed, episodic and working memory, visuospatial skills, executive functions, and fine and gross motor skills [1, 2] and is associated with global cerebral atrophy (brain degeneration). However, some regions, such as the prefrontal cortex and the hippocampus, are more affected than others [3, 4].

Executive functions are one of the cognitive domains most affected by aging [5, 6], and especially so in MCI patients [7–12].

### Training regimens to countervail age-related cognitive decline

Evidence suggests that regular cognitive training [13–15] can boost or maintain cognitive and brain functions known to decline with age. Such cognitive training is most often administered on a computer and in a lab setting and far transfer effects to non-trained domains are scarce [16–19]. Yet, training regimens that can be integrated into activities of daily living, such as musical practice [20, 21], dancing [22], playing chess [23] or physical exercise [24–27], might be more effective. Their complex and variable nature may induce transfer effects to different cognitive domains more efficiently [28, 29], and moreover, increase motivation [4, 25, 30], allowing maintaining these activities in the long term (over several years). However, only a direct comparison of regimens that can be integrated into daily activities versus training in a laboratory setting (computerized or not), of comparable duration and intensity, with a number of patients providing sufficient statistical power, could yield a well-founded answer to this presumption. This should be investigated in future research.

Instrumental musical training seems to confer certain advantages over other types of exercise [21, 31–33]. Playing an instrument directly involves both core cognitive components, such as working memory, attention, processing speed, and executive functions, and also abstract reasoning [34]. The multimodal nature of musical performance may represent one of the explanations of its efficacy, as auditory, sensorimotor, proprioceptive, and visual feedback are put into relationship with the expected acoustic musical end product and also with the music score to correct and refine the motor performance [35], interconnected by memory functions, executive functions and abstract reasoning [36].

Moreover, the auditive aspect is unique to music-making and processing. Among all sensory systems, the auditive one is the fastest [37]. This ultrafast processing in a dynamic setting may thus drive the subcomponents of WM updating, i.e. temporal sequencing and monitoring [38].

Then, in contrast to gross motor functions implicated in psychomotor therapy, fine sensorimotor skills play a crucial role in playing a musical instrument, including bimanual coordination.

Finally, music-making's emotional and rewarding aspects represent an intrinsic motivator underpinned by neurochemistry (e.g., dopamine release) [39–41]. Musical activities also impact other physiological processes, inciting potential positive effects on the cardiovascular system (cortisol decrease) and increasing stamina (dopamine increase), via neurochemistry [39, 41, 42].

Musical training performed during youth or midlife positively influences cognitive reserve (resilience to neuro-pathological damage in older adults) [43–45], and may delay the onset of dementia [46, 47]. Improved executive function, well-being, visual memory, and hearing in noise manifested in healthy older adults after musical training starting at an advanced age [20, 21, 33, 48]. Several recent studies [49–52] could show advantages following musical training after retirement in healthy older adults, associated with brain changes, for certain capacities implied in activities of daily living (speech in noise perception, verbal memory, and manual dexterity). Musical training thus seems a promising approach.

Physical training also represents a favorable approach in the fight against pathological decline, defined as a loss of cognitive capacities beyond normal aging [53]. Aerobic training positively influences cognitive function in the elderly [25–27, 54]. It may even retard dementias like Alzheimer's disease [55]. Although less acknowledged, cognitive and sensorimotor benefits also showed following non-aerobic exercises, like Baduanjin, Tai Chi, or psychomotor training [56–58], that instead involve slow non-aerobic movement. Yet this type of physical intervention seems better suited for frail older adults than aerobic exercise.

Recent evidence shows that psychomotor treatment, pertaining to the so-called body-mind approaches, may also positively influence physical, cognitive, and emotional functioning in healthy elderly [59]. A 6-months Randomized Controlled Trial (RCT) using Norwegian physical psychomotor therapy conducted in 105 adults (18–70 years old) [60] showed considerable improvement of health-related quality of life evaluated by questionnaires (physical functioning, general and mental health, emotional issues, social functioning, self-esteem, etc.). Notably, in healthy elderly, psychomotor interventions induced cognitive (processing speed, executive functioning, and attention) and physical benefits for gross motor control (improvements in balance, gait, and mobility), after only 10–12 weeks of training [58]. The latter is vital as fall risk increases in MCI patients [61]. Like musical practice, psychomotor practice thus represents a good candidate for non-medical interventions aiming to countervail normal and pathological mental decline in the elderly.

Two RCTs applying musical interventions on MCI patients [62, 63], showed positive effects on verbal fluency, attention, executive functions and praxis (Clock Drawing test), on a general cognitive test (MMSE; Mini-Mental State Examination) [64] and mood. The musical training involved vocal and instrumental improvisation and was compared to soft gymnastics training (active control condition); both lasted 3 months. The control group, however, received much shorter training sessions. Two recent systematic reviews [65, 66] showed a significant positive effect of active music-making and other music-based interventions on cognitive functioning in patients with MCI and dementia.

A recent review by Cespon et al. [67] postulates that MCI patients profit most from multimodal programs, combining cognitive and physical stimulation. Cespon et al. divide non-invasive interventional approaches into cognitive interventions and physical exercise. The 2 non-aerobic interventions proposed here comprise elements of both and thus constitute such multimodal activities. Psychomotor exercise involves gross motor control (gait, balance, mobility) and also stimulates cognitive functions. Music instrumental practice taps directly into cognitive functions, particularly executive functions, but also drives fine motor control (manual dexterity, bimanual coordination, upper limb resistance), and neurochemistry.

Concerning brain plasticity, 2 recent RCT trials used structural and functional Magnetic Resonance Imaging (MRI) to assess the efficacy of treatments on MCI patients [68, 69]. Simon and colleagues [68] compared mnemonic strategy training over 2 weeks to an active control group of MCI patients who followed an educational program. Neuropsychological tests and functional MRI (fMRI), the latter using a Face-Name Recognition Task, were measured before and after training. MCI patients in the training group showed improved face-name memory and higher fMRI activation in the left anterior temporal lobe. No indication of far transfer occurred. The experimental group's face-name memory task demonstrated preserved improvement after one and three months. The "Train the Brain" consortium [69] compared the effects of combined 7-month physical-cognitive training to a passive control group on cognitive decline, gray matter volume, cerebral blood flow (CBF) in hippocampal areas, and fMRI activity elicited by a cognitive task. Cognitive status significantly improved in the training group whereas it decreased in the control group. In the training group, parahippocampal CBF increased. Both studies [68, 69] show that non-pharmacological interventions may improve cognitive functioning and brain health in MCI patients.

Mild Cognitive Impairment (MCI) represents a cognitive state between normal aging and dementia, with a minor age-related loss of cognitive ability that does not importantly impact daily life functioning. Symptoms most frequently involve impairments in memory, attention, spatial orientation, executive functions [70–72]. Increased fall risk is an associated condition [61].

Although some MCI patients may stay stable or even recover to some extent [73], some of them are on a downward slope to overt dementia, i.e., a pathway of no return [73, 74].

### Main hypothesis

We anticipate that, compared to changes in the healthy control group, 6 months of intensive musical practice or psychomotor training will distinctively reinforce general cognitive and physical functioning of MCI patients. Overall, we anticipate that musical instrument practice will have a significantly more profound impact.

### Theoretical framework

Our approach is based on an emerging field of evolutionary medicine investigating the effects of lifestyle on health and well-being [75]. Apparently, moderate intensities of physical exercise with a simultaneous cognitive load seem associated with human evolutionary history [76]. The adaptive capacity model (ACM) [76], presumes that lifestyle changes, which combine the benefits of moderate physical exercise and novel cognitive challenges may provoke neuroplasticity most strongly and therefore provide neuroprotection against aging. Musical practice and psychomotor training both comprise such a combination of moderate-intensity physical with cognitive training. Moderate-intensity physical exercise seems to provide the strongest cognitive benefits in humans [77]. This neuroprotection, potentially resulting in an increase of cognitive reserve or resilience, may then contribute to psychological well-being (mental health) [78]. More research is needed to confirm this postulate [76].

### Goals

With this project, we hope to generate new scientific knowledge on the effectiveness of non-medical therapies that involve moderate physical exercise and cognitive stimulation, to improve the mental, physical and cerebral health of MCI patients.

If the results turn out positive, the autonomy, well-being, and quality of life of these patients and their caregivers might be enhanced, and the risk of developing Alzheimer's disease or another type of dementia delayed or reduced.

If so, the study could serve as a springboard for developing and implementing innovative, targeted musical and psychomotor or other non-medical interventions for different types of pathological populations with cognitive impairment in the context of population aging. In addition, these interventions will be less costly than more traditional treatments.

### Rationale

Cognitive decline represents a major threat among the deleterious effects of population aging. We propose to conduct an RCT on MCI patients and investigate whether intensive musical or psychomotor group interventions can improve their cognitive and sensorimotor functioning and induce brain plasticity compared to a passive control group of healthy matched individuals.

Longitudinal applied neuroscience studies on non-medical interventions are still rare, although particularly interesting in the early stages of pathological decline, when a reverse tendency may still be provoked. Moreover, by incorporating brain data, we can gain a more comprehensive understanding of those early-stage mental disorders and their potential development.

To optimize the learning process, we offer intensive training regimens: music practice and psychomotor treatment interventions take place twice a week over 6 months, provided by professionals in each field (holding a Master degree), completed by daily homework.

To accurately monitor development, assessments take place before (baseline), at mid-term and immediately after the interventions. Cognitive and sensorimotor development is assessed through a battery of psychometric tests, including an evaluation of well-being and autonomy in daily life. To evaluate concurrent brain plasticity, functional and structural Magnetic Resonance Imaging (MRI) measurements are performed at the same time points.

### Aims

This RCT aims to determine if 2 specifically developed innovative behavioral non-medical experimental interventions over 6 months, i.e. intensive musical instrumental practice and psychomotor interventions in small groups may have an important societal impact, via the reduction or stabilization of cognitive, sensorimotor and cerebral decline, in MCI patients compared to a passive control group, composed of healthy matched controls (from now on: passive control group).

### Hypotheses and outcomes

### Main hypothesis

We hypothesize that 6 months of intensive musical practice or psychomotor training will improve or stabilize -each in their own way- general cognitive and physical functioning of MCI patients, compared to the passive control group. Altogether we expect a far stronger effect of musical instrumental practice.

### Comparisons

To evaluate our outcomes, we will compare the development in each experimental group of MCI patients over time, to the development in the passive control group over time. We will also compare the development over time between the 2 experimental groups (see the section Specific outcomes according to each intervention). As we are interested in development, we will incorporate the baseline scores in our statistical models, to correct for differences at baseline. All groups, the passive control group included, may show test–retest effects over time.

### Primary Outcome

The primary outcome is increase of the total weighted score at the COGTEL test^1^ [79, 80] at mid-term, after 3 months (t1) and after 6 months (t2) of interventions in the musical practice group and/or the psychomotor practice group of MCI patients compared to baseline and to the passive control group.

The COGTEL served as primary outcome in several recent clinical and epidemiological studies [81–85].

### Choice of the COGTEL

Although the COGTEL weighted score and the Mini-Mental State Examination (MMSE) [64] correlate at 0.93 [80], the COGTEL covers more cognitive domains (n = 6) than traditional screening tools like the MMSE, which is rather a dementia screening. It comprises 6 subtests covering prospective memory, short- and long-term verbal memory, working memory (digit span), verbal fluency and inductive reasoning.

The COGTEL thus allows a more fine-tuned analysis of cognitive abilities [86]. In addition, test–retest reliability is good (r = 0.85) [80].

### Secondary hypotheses

We hypothesize that the 2 experimental interventions over 6 months in MCI patients, will improve basic cognitive and executive functioning, compared to the passive control group that will stay stable or regress.We hypothesize that the 2 experimental interventions over 6 months in MCI patients, will improve sensorimotor functioning, compared to the passive control group that will stay stable or regress.We hypothesize that functional and structural brain plasticity associated or not with cognitive and sensorimotor benefits will occur over 6 months in the 2 experimental groups of MCI patients, compared to the passive control group that will stay stable or regress.We hypothesize that daily living activities will improve over 6 months in the 2 intervention groups of MCI patients, compared to the passive control group that will stay stable or regress.We hypothesize that subjective well-being will improve in the 2 intervention groups of MCI patients over 6 months, following the regular social interactions and structured activities during the interventions and at home [87], compared to the passive control group that will stay stable or regress.

### Secondary Outcomes

Improve basic cognition and executive function functioning in the 2 experimental intervention groups of MCI patients over 6 months, compared to the passive control group, measured by the scores of the following cognitive tests: individual subtests of the COGTEL [79, 80], d2-R test [88, 89], Trail Making tests [90], Go/No-Go [91], visual working memory (fMRI test) [92] and Clock Drawing test^2^ [93].Improve sensorimotor functioning in the 2 experimental intervention groups of MCI patients over 6 months, compared to the passive control group, measured by the individual and total scores of the sensorimotor tests: Clock Drawing test [93], Purdue Pegboard [94], Unipedal balance test [95] and Laterality recognition test [96].Induce functional and structural brain plasticity and connectivity associated or not with cognitive and sensorimotor benefits in the 2 experimental intervention groups of MCI patients over 6 months, compared to the passive control group, measured by structural, resting-state functional, functional and DTI (Diffusion Tensor Imaging) MRI.Improve daily living activities as measured by the Amsterdam Instrumental Activity of the Daily Living Questionnaire [97] in the experimental groups of MCI patients over 6 months, compared to the control groupImproved subjective well-being in the 2 experimental groups of MCI patients after 6 months, compared to the control group, measured by the World Health Organization Quality of Life-BREF questionnaire (BREF for abbreviated) (WHOQOL-BREF) [98].

### Specific outcomes according to each intervention 

#### Music practice intervention

Instrumental musical training seems to confer advantages over other types of training in children [32, 99] and elderly [21, 33] and specifically so in MCI patients [62, 65]. Playing an instrument requires both core cognitive components, such as working memory, attention, or processing speed [20, 99, 100], and complex components such as executive functions and even abstract reasoning [20, 21, 34, 101]. Therefore we expect greater advantages in the music group compared to the psychomotor group for the weighted COGTEL score, individual subtests of the COGTEL [79, 80], d2-R test [88, 89], Trail Making tests [90], Go/No-Go [91], visual working memory (fMRI test) [92] and Clock Drawing test [93] (corresponding to Secondary Outcomes no. 1). In addition, sensorimotor function and coordination of the upper body and the hands play a major role and may increase in this group as compared to the psychomotor and control group (Clock Drawing test), Purdue Pegboard test [101, 102]. Emotion regulation may also be enhanced [103], and indirectly impact executive functions.

Functional and structural brain plasticity associated with cognitive and sensorimotor benefits may show in the prefrontal cortex [104–106], the hippocampus [4, 34, 107–109] and sensorimotor areas [110–114], including the auditory cortices [104, 115–117] and also by enhanced functional and structural connectivity [50, 51, 118, 119].

#### Psychomotor intervention

Cognitive benefits such as reinforced processing speed, attention, and executive functions [58, 59, 120] but also emotion regulation [121] and visuospatial memory [120] may occur in this group, but we expect less strong benefits than in the music group for the weighted COGTEL score, individual subtests of the COGTEL [79, 80], d2-R test [88, 89], Trail Making tests [90], Go/No-Go [91], visual working memory (fMRI test) [92] and Clock Drawing test [93] (Secondary Outcomes no. 1). However, whole body sensorimotor function, balance, and body schema representation may improve more strongly following psychomotor interventions, compared to the music practice and the control group, as was shown for coordination training, Pilates and other body-mind approaches [120, 122, 123], and specifically for psychomotor training [58, 124]. Therefore, scores on the Unipedal balance test, and the Laterality recognition test may be enhanced compared to the music group. As no studies exist measuring brain plasticity following psychomotor training, we can not specify brain plasticity effects citing the literature. Still, they may overlap to some extent with those observed for music practice, concerning the prefrontal cortex and sensorimotor areas. Sensorimotor activity will more likely implicate areas that involve the whole body, and act on associated functional and structural connectivity [125].

## Methods & design

Our study consists of an extension of the study by Biasutti and Mangiacotti, 2018 [62] on music practice in MCI patients as compared to soft gymnastics. However, we will opt for a more comprehensive approach changing the following elements with respect to the experimental design of Biasutti and Mangiacotti, 2018: 1) our psychometric measures will not only involve cognitive tasks, but also sensorimotor performance, activities of daily living and well-being, 2) importantly, in addition, we will collect different functional and structural brain imaging data, 3) instead of soft gymnastics as a control group, we added psychomotor practice, a body-mind approach, as a second experimental intervention, 4) our study will be more extended over time (6 months against 3 months for [62]), and 5) both experimental interventions strongly involve sensorimotricity, often weakened in this population [61, 72], 6) in the current study, we will essentially train the music groups to learn and produce existing musical excerpts together, thus enhancing memory functions, although some improvisation will be included in the interventions, 7) our intervention groups will be small (n = 3–4, against n ~ 20 in [62]), permitting sufficient personal attention from the teachers for each participant, and meanwhile allowing group dynamics in order to strongly implicate executive functions (inhibition, working memory, planning, etc.) and attention, that are key targets for stimulating cognitive reserve, 8) comparing psychomotor to music practice interventions will allow to disentangle whole body sensorimotor from hand and arm sensorimotor aspects, and to detect domain specific cognitive and emotion related effects of each regimen, 9) a passive healthy control group will control for age-related natural brain atrophy and test–retest effects of the psychometrics and fMRI tasks.

Thus, the current study introduces numerous novel features. Please see the section "Innovative Aspects” in the Discussion Section for a comprehensive overview.

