## Statistical analysis plan and sample size calculation

### Basic statistical analyses

First we will use linear mixed model equations (lme) using the open-source software R [144] to evaluate the longitudinal effects for all variables separately comparing both experimental groups to the control group and to each other. These lme are flexible and powerful statistical models that consider several levels of clustering, continuous, ordinal and categorical explanatory variables. They support unbalanced data and allow to integrate demographic data into the models. Our 2 patient groups may turn out unbalanced due to attrition. Moreover, because we are interested in development, we will incorporate the baseline scores in the models. This will allow correcting for differences between the groups at baseline.

We will also compare those results with more traditional multivariate analyses of covariance.

If the data are not normally distributed, and if data transformation cannot cope with this non-normality, we will either use robust analyses (weighting outliers or other influential observations) or use non-parametric approaches.

In testing multiple contrasts, adjustments of the alpha criterion for multiple comparisons will be applied.

Concerning the primary objective, the analysis will consist in evaluating increase or less decrease (experimental group 1 or 2 vs. the control group) of the total weighted score at the COGTEL test [79, 80] at t1 and t2 compared to baseline and to the passive control group, by means of lme and MANCOVA analyses, using a two-sided alpha criterion of 0.05.

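### The claim to separate whole-body from hand and arm effects has no defined test behind it: each variable is modelled separately and no arm-by-test interaction is stated

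*Protocol article*

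**What the plan says.** In Methods & design, element 8 of the list of changes from the earlier music trial states that "comparing psychomotor to music practice interventions will allow to disentangle whole body sensorimotor from hand and arm sensorimotor aspects".

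The predictions behind it are crossed. Under Music practice intervention, "sensorimotor function and coordination of the upper body and the hands play a major role and may increase in this group", relative to the psychomotor and control groups, with Clock Drawing and Purdue Pegboard as the measures. Under Psychomotor intervention, "scores on the Unipedal balance test, and the Laterality recognition test may be enhanced compared to the music group".

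Under Basic statistical analyses, linear mixed models are used "to evaluate the longitudinal effects for all variables separately comparing both experimental groups to the control group and to each other". Two additions follow: "We will also compare those results with more traditional multivariate analyses of covariance", and "In testing multiple contrasts, adjustments of the alpha criterion for multiple comparisons will be applied". The Discussion mentions contrasts and conjunction analyses for overlapping and specific benefits but defines no model for them. Advanced multivariate statistical analyses describes ICA and PLS work, which it calls exploratory.

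**The concern.** To say that two kinds of sensorimotor effect have been separated is to say that the music-versus-psychomotor difference on a hand test is not the same as the difference on a whole-body test. Statistically, that is an arm-by-test interaction. One model per variable gives an arm effect and a p-value for each test, but no estimate or test of how far those effects differ.

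If Purdue Pegboard is significant and Unipedal balance is not, the two arm effects may still be equal. In small arms that outcome is common whether or not a dissociation exists. Music versus psychomotor is the only randomised comparison in the trial (Study design), so this is where a claim about what each training specifically does would carry most weight. At stake are a possible false claim of specificity and low power for the authors' own prediction.

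**Working it through.** **The plan's own figure.** Statistical power of the study takes partial eta squared 0.296 from an MMSE result. f = sqrt(0.296 / 0.704) = 0.648, which the article rounds to 0.65; for two groups d = 2f = 1.3. A two-group F test with alpha 0.05 and power 0.80 needs 11 per group. At the stated 12 per group, power is 0.86. The figure is close and is not disputed here. It is the only effect size in the article, and none is given for any sensorimotor test.

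**Inputs from the article.** About 16 patients per arm (Study design); a minimum of 12 completers per group (Attrition / Drop-outs); two-sided alpha 0.05, stated for the primary objective.

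**Inputs assumed, because the article gives none.** Standardised, normally distributed change scores on two tests; between-test correlation r = 0 to 0.5; arm differences of 0.5, 0.6, 0.8 and 1.3 SD; no clustering by training group.

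**Tests compared.** (a) A two-sample t test on each outcome at 0.05. (b) A t test between arms on the within-patient difference of the two standardised scores, which is the arm-by-test interaction. There were 40,000 simulated trials per setting.

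**Arithmetic at r = 0.**
- Equal 0.5 SD advantage, 12 per arm: the power of one test is p = 0.216. The chance that exactly one of two is significant is 2p(1 - p) = 2 × 0.216 × 0.784 = 0.34. With 16 per arm, p is about 0.276, giving 2 × 0.276 × 0.724 = 0.40.
- Crossover of ±0.6 SD: the arm effects differ by 1.2 SD. The within-patient difference has SD sqrt(2(1 - r)), so the interaction effect is 1.2 / sqrt(2) = 0.85 SD at r = 0 and 1.2 / 1 = 1.2 SD at r = 0.5. Each single test works with only 0.6 SD.

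**Results over 12-16 per arm and r = 0 to 0.5.**

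| True state | Separate tests at 0.05 | Interaction significant |
|---|---|---|
| Equal advantage 0.5 SD (no dissociation) | exactly one significant: 25-40%; Pegboard only: 12-20% | about 5% |
| Equal advantage 0.8 SD (no dissociation) | exactly one significant: 33-50%; Pegboard only: 16-25% | about 5% |
| Crossover ±0.6 SD | both significant as predicted: 4-14% | 51-91% |
| Crossover ±0.8 SD (r = 0 to 0.3) | both as predicted: 17-35%; exactly one: 48-58% | 75-96% |
| Crossover ±1.3 SD | both as predicted: 73-89% | little left to gain |

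**Alpha adjustment.** The article names no method, so two illustrations follow. At 0.025 per test, exactly one is significant in 18-31% (equal 0.5 SD) or 32-50% (equal 0.8 SD), and both are significant under the ±0.6 SD crossover in 1-7%. With Bonferroni over four tests, the Pegboard-only pattern falls to 6-11% (0.5 SD) and 14-23% (0.8 SD).

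**Do the other named analyses fill the gap?** The usual arm effect in a MANCOVA asks whether the arms differ on any outcome, so an equal advantage on every test would also reject it. Alpha adjustment controls error test by test and does not compare effects between tests. A conjunction addresses overlap between interventions. The contrasts in the Discussion come closest in intent but are undefined. ICA and PLS are exploratory.

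**The case against.** The strongest reply is that the article contains no faulty reading rule. It sets out direct music-versus-psychomotor comparisons with opposite predictions. If both are significant as predicted, that is valid evidence of a dissociation, and with equal effects it arises by chance in under 0.1% of trials. This stands. What remains is that at ±0.6 SD this valid route succeeds in only 4-14% of trials.

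The magnitude also depends on assumptions. The 25-40% counts both orders, and the order that matches the hand-specific prediction is about half of it. The scenario has music helping balance as much as dexterity, which the article does not expect; with no effect on either test, the Pegboard-only pattern occurs in about 2%. At d = 1.3 the separate tests do well. All of this stands and limits the size of the point.

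The exact contrast might be in an analysis plan that is not shown. That would excuse a missing detail. But the article itself fixes the unit of analysis as one variable at a time and states flatly what the arm comparison will allow.

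A reader might infer three stronger points that the documents do not support:
- That a discordant pair would be reported as a dissociation. No section says so; it only could be.
- That a sensorimotor total would cancel the opposite effects. Secondary Outcomes does speak of scores "measured by the individual and total scores of the sensorimotor tests", but for comparison with the passive control group; no cross-test total is planned for music versus psychomotor.
- That the domain-specific wording in element 8 is at fault too. It is attached to cognitive and emotion-related effects, which a hand-versus-balance interaction does not address.

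**Conclusion.** The point holds in limited form. Element 8 promises a separation of whole-body from hand and arm aspects, and no stated analysis tests whether the arm effect differs between the two kinds of test. Under the assumptions above, a discordant pair cannot tell the two situations apart: it is common with equal effects and is the most frequent single result under a true ±0.8 SD crossover. The interaction keeps its error near 5% and has clearly more power for moderate crossed effects, with the advantage shrinking as effects grow. The percentages rest on assumed effects and correlations and, except where stated, on unadjusted alpha. The aim is secondary: it appears in a list of design features, not among the Aims, the hypotheses or the Secondary Outcomes, and the predictions are hedged. The change is worth making because it is cheap and serves the authors' own prediction.

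**What to change.** In the two randomised arms, pre-specify one baseline-adjusted mixed model at t2 on standardised scores of the sensorimotor tests named in the two intervention-specific sections: at least Purdue Pegboard and Unipedal balance, and preferably Clock Drawing and Laterality recognition too. Code every test so that higher is better, use a random patient effect, and include an arm-by-test interaction. Report the arm effect on each test with its confidence interval.

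Make the separation statement for hand versus whole-body function only if the interaction is significant and the arm effects lie in the predicted directions. The second condition is needed because music being better on both tests, but more so on one, would also give an interaction. Otherwise, limit element 8 to a comparison of two training packages.

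The cost is some plan wording and one extra model on data already being collected. The small downside is that the result is in SD units and depends on the chosen scaling, which should therefore be fixed in advance, for example on the pooled patient baseline.
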